### Secondary study parameters

Secondary outcomes of this study are: to determine any between group differences in self-reported functional outcomes, clinimetrics and development of osteoarthritis at 6 week, 3, 6 and 9 months, 2, 5 and 10 years after surgery and secondly, whether between groups differences exist, both with respect to perioperative classification of the ACL rupture type and onset of failure of the ACL repair or reconstruction.

Differences in baseline characteristics will be recorded by the use of IKDC 2000 demographic form, IKDC 2000 Current Health, IKDC 2000 History and reported complications and side effects.

Patient self reported outcomes will assess the patients’ perceived level of functional recovery (IKDC Subjective Scale) [23–25], daily life activities (Knee Injury and Osteoarthritis Outcome Score (KOOS)) [26], level of physical activity (Tegner Activity Level) [27, 28], knee pain (Visual Analogue Scale (VAS)) and satisfaction with the outcome of surgery. Clinimetrics will be assessed by the IKDC 2000 physical examination score [23–25], including instrumented anteroposterior laxity (Rolimeter) [29–32] as well as leg symmetry index (LSI) for Gustavsson’s jump test battery and isokinetic quadriceps and hamstrings force measured by a dynamometer (Isoforce) [33].

Additional secondary outcomes are knee kinematic parameters (i.e. degree of flexion and varus/valgus angles) 1 and 2 year(s) after surgery; the jump tests will be instrumented and patients will be equipped with inertial sensors (Xsens Technologies) for these tests. Furthermore, in order to explore the role of long lasting exertion (one-hour running and pivoting protocol) on neuromuscular fatigue and knee kinematics, a sport-specific fatigue test with EMG measurement of quadriceps and hamstring activity, and inertial biomechanical sensors to measure functional biomechanical parameters (Xsens Technologies) will be performed in a subgroup 1 year after ACL suture repair.

Two independent radiologists will evaluate the Kellgren and Lawrence score for radiologic signs of osteoarthritis on anteroposterior and lateral weight baring X-rays [34].

Failure, defined as the occurrence pathological laxity or subjective instability, or the discontinuity of the ACL suture repair or reconstruction based on MRI or arthroscopy, as well as other complications will be recorded. Also, perioperative classification of ACL rupture type (tear location (proximal, midsubstance, distal rupture), rupture pattern (single strand, two bundles, three or more strands), and synovial sheath (completely intact, > 50% intact, < 50% intact)) [20] as well as perioperative classification regarding quality of the repair (anatomical, nearly-anatomical, non-anatomical) will be assessed [35].

### Randomization

After inclusion, patients will be randomized into an experimental group (repair) or a control group (reconstruction), in blocks with varying sizes (*N* = 2 and *N* = 4) by an independent investigator with PASS (Power Analyses and Sample Size Software; rand.exe version 6.0). The extent of physical activity in daily life poses a potential risk to repair/graft failure. To make sure both groups have an equal risk of failure, patients will be stratified based on physical activity level using the Tegner score (moderate: Tegner 5-7; high: Tegner 8-10) [27, 28].

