### Study sample

Patients eligible for enrolment in this study are sportively active patients between 18 and 30 years with a proven primary ACL rupture, confirmed by means of history, physical examination and MRI, for whom an indication for ACL reconstruction surgery exists and who can undergo surgery within 21 days of injury. Exclusion criteria are concomitant large meniscal injury needing repair, cartilage injury requiring surgical intervention or ligamentous lesions of the ipsilateral knee, pre-injury Tegner score below 5, history of knee surgery of the ipsilateral knee, pre-existing significant malalignment of the ipsilateral knee, hypersensitivity to cobalt, chromium or nickel, muscular, neurological or vascular abnormalities, osteoarthritis, use of prednisone or cytostatics, tendency to form excessive scar tissue, pregnancy, osteoporosis or infection.

Patients can withdraw from the study at any time. They will receive appropriate treatment according to standard-care.

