### Sample size determination

In order to detect non-inferiority of ACL repair compared to ACL reconstruction surgery in terms of patient self-reported functional outcome measured by the IKDC Subjective score, to achieve a power of 90% and an alpha of 5%, a sample size of 20 patients in each study group is required. According to literature, it seems relevant to consider a standard deviation at nine in both groups [36]. A difference of 11, 5 points in score of IKDC 2000 is suggested as clinically relevant [37]. The margin of equivalence 10 lies within this clinically relevant effect size.

Considering a lost-to-follow-up rate of 20%, it is planned to include 24 patients per randomization group. Thus, in total 48 patients will be included in the study.

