#### Primary study parameter

Differences between IKDC 2000 at baseline and one-year post-operative will be determined for each group, as well as differences between the groups at each follow-up. In case of clinically meaningful differences between groups (> 10 points on the IKDC2000), the non-inferiority hypothesis will be rejected. In case of non-inferiority, superiority analyses will be conducted. For normally distributed data mixed models analyses for repeated measures will be used. In case of non-normally distributed data, the Friedman test for differences within groups, and Mann-Whitney Y test for differences between groups, will be used. A distinction will be made between short term (6 weeks, 3, 6, 9 months and 1 year), mid-term (2 and 5 year) and long-term (10 year) postoperative outcomes.

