#### Secondary study parameters

For IKDC 2000, KOOS, Tegner, VAS, IKDC 2000 physical examination, AP-laxity, LSI for jump tests, isokinetic quadriceps and hamstring force as well as re-rupture, the same statistics as described above will be used. Re-rupture of 10% or more is considered to be clinically relevant. For the sport-specific fatigue protocol repeated measures ANOVA with SIDAK t-test post hoc test will be performed.

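### Allocation is stratified by Tegner level, but no stated analysis names the stratum and the plain Mann-Whitney fallback cannot carry it; the cost is modest and conservative

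*Protocol article*

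**What the plan says.** The Randomization section of the protocol article allocates patients in blocks of 2 and 4, and "patients will be stratified based on physical activity level using the Tegner score", with levels 5-7 (moderate) and 8-10 (high). The lower bound matches the eligibility rule, which excludes a "pre-injury Tegner score below 5". The reason given is "To make sure both groups have an equal risk of failure"; precision is not mentioned.

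The Primary study parameter section names two routes. The first is "For normally distributed data mixed models analyses for repeated measures will be used", with no fixed effects or covariates listed. The second is "In case of non-normally distributed data, the Friedman test for differences within groups, and Mann-Whitney Y test for differences between groups, will be used". The Secondary study parameters section covers the other scores, the clinical measurements and re-rupture with one phrase: "the same statistics as described above will be used". The Tegner stratum appears in none of these sentences.

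**The concern.** Stratified blocks make the two groups alike on Tegner level, so the true sampling variation of the group difference no longer contains the between-stratum part. An analysis that ignores the stratum still counts that part as error. Its standard error is then too large whenever the stratum predicts the outcome, and the interval compared with the 10-point margin is wider than it need be.

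Balance is also secured only at allocation. The two Intervention subsections remove patients who are found at arthroscopy to meet an exclusion criterion. That happens after randomisation and at different times by arm: within 21 days of injury for repair, usually about 6 weeks for reconstruction. The Sample size determination section expects a further 20% to be lost. The patients analysed may therefore differ in Tegner mix, and no stated analysis corrects for it.

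At stake is some precision in a trial with about 20 evaluable patients per group.

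**Working it through.** **Inputs from the article (Sample size determination).** SD 9 in both groups, margin 10, power 90%, alpha 5%, 20 evaluable and 24 randomised per group. Sidedness is not stated; one-sided 0.025 is assumed here.

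**Input not in the article.** R², the share of 1-year IKDC variance explained by the stratum. It is taken as a range from 0 to 0.20.

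**Step 1: reproduce the plan's figure.** n per group = 2 × [SD × (z₀.₉₇₅ + z₀.₉₀) / margin]² = 2 × [9 × (1.960 + 1.282) / 10]² = 17.02, so 18, or 19 with the noncentral t distribution. The stated 20 is within 2 patients of this. (One-sided 0.05 would give 14, or 15 by t.) The formula uses the full SD of 9, so the plan counts on no gain from the stratum. With a true difference of zero, 20 per group and no stratum term, power is 92.8% by t. The allowance for losses is 20 × 1.2 = 24.

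**Step 2: what R² means in IKDC points.** With two equal strata and total SD 9, the gap between strata is 2 × 9 × √R². This is 4.0 points at R² = 0.05, 5.7 at 0.10 and 8.0 at 0.20.

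**Step 3: analysis without and with the stratum.** Simulation with 40,000 runs per setting: 20 per group, two equal strata, 1:1 within stratum, t test of the group difference at one time point, one-sided 0.025. Each cell gives the result without / with the stratum term.

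| R² | CI half-width | Power, % | Type I error at the margin |
|---|---|---|---|
| 0 | 5.71 / 5.72 | 92.8 / 92.8 | 0.026 / 0.026 |
| 0.05 | 5.73 / 5.59 | 93.3 / 94.0 | 0.023 / 0.026 |
| 0.10 | 5.74 / 5.44 | 93.9 / 95.1 | 0.019 / 0.025 |
| 0.20 | 5.75 / 5.12 | 94.5 / 96.8 | 0.014 / 0.025 |

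The Monte Carlo standard error of a type I error near 0.025 is √(0.025 × 0.975 / 40,000) ≈ 0.0008.

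- Half-width at R² = 0.10: 1 − 5.44/5.74 = 5% narrower. At R² = 0.20: 1 − 5.12/5.75 = 11% narrower.
- Power gain: 95.1 − 93.9 = 1.2 points at R² = 0.10, and 96.8 − 94.5 = 2.3 points at R² = 0.20.
- Power without the stratum term rises with R² because balanced allocation has already removed the between-stratum variation from the difference itself. Only the estimated standard error fails to reflect this, which is why the type I error falls below 0.025.

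**Step 4: imbalance after allocation.** As an illustration, suppose 12 of 20 analysed patients in one group and 8 of 20 in the other are in the high stratum. The unadjusted difference shifts by (0.6 − 0.4) × 5.7 = 1.1 points at R² = 0.10, or 0.2 × 8.0 = 1.6 points at R² = 0.20, in either direction, against a margin of 10. A stratum term removes that shift.

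**The case against.** The strongest reply is that the article names only a class of model. It lists no covariates at all, so its silence does not exclude the stratum, and a covariate list is commonly left to a full protocol or analysis plan that is not shown here. That stands for the mixed model, where the right request is confirmation. It does not cover the fallback: Mann-Whitney is named as the between-group test, and in its plain form it has no place for a stratum.

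A reader might infer that the plan throws away precision that the stratification was meant to buy. The article does not say so. Its stated aim is equal failure risk, and stratified blocks deliver that at allocation whatever the analysis does.

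A reader might also infer that the trial is underpowered without the stratum, since a variance ratio of 1/(1 − R²) corresponds to 5% to 25% more patients for R² of 0.05 to 0.20. That does not follow either. The sample size was set with the full SD, and power without the stratum term is already above the 90% target.

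Finally, the article gives no link between Tegner level and IKDC. Entry is already limited to active patients aged 18 to 30, and the top of the assumed range needs an 8-point gap between strata against an SD of 9. A gain of zero is possible, and the range must include it.

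**Conclusion.** The point holds as a modest improvement. The stratum governs the randomisation, no stated analysis names it, and the rank-test fallback as written cannot use it. For an assumed R² of 0 to 0.20, the precision forgone is 0 to about 11% of the interval half-width and 0 to about 2.3 percentage points of power. Tegner imbalance from losses and exclusions would also go uncorrected.

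The omission does not raise the risk of a false non-inferiority claim: with balanced strata the type I error without the stratum term is 0.019 at R² = 0.10 and 0.014 at R² = 0.20, against 0.025 nominal. Nor does it reduce the planned power.

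These figures rest on one-sided 0.025, equal strata, 20 evaluable per group and a single-time-point comparison in place of the full repeated-measures model. A stratum term corrects Tegner imbalance only, and not any other effect of exclusions made after randomisation.

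**What to change.** State before the data are analysed that the mixed model for IKDC and the other continuous outcomes includes the Tegner stratum as randomised (5-7 versus 8-10) as a fixed effect, or confirm that the full protocol already says so. Replace the plain Mann-Whitney fallback with the stratified van Elteren test.

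Stratifying the re-rupture comparison is optional and depends on event numbers. At the 10% rate that the article treats as clinically relevant, 20 patients give 2 events per group, which may be too few to split.

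The variable is already collected. The cost is one degree of freedom (37 in place of 38 in a two-group comparison of 20 each), and if Tegner level predicts nothing the half-width changes only from 5.71 to 5.72.

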### Sample size determination

In order to detect non-inferiority of ACL repair compared to ACL reconstruction surgery in terms of patient self-reported functional outcome measured by the IKDC Subjective score, to achieve a power of 90% and an alpha of 5%, a sample size of 20 patients in each study group is required. According to literature, it seems relevant to consider a standard deviation at nine in both groups [36]. A difference of 11, 5 points in score of IKDC 2000 is suggested as clinically relevant [37]. The margin of equivalence 10 lies within this clinically relevant effect size.

Considering a lost-to-follow-up rate of 20%, it is planned to include 24 patients per randomization group. Thus, in total 48 patients will be included in the study.

### Statistics

The identified data will be entered into and analysed with SPSS version 23 (IBM SPSS, Chicago, Illinois, USA) by the trialcoordinator who is not involved in data collection and therefore not blinded to group allocation of participants. Trial results will be published in scientific journals.

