## Methods

### Study design

This study is a Medical Ethical Committee approved, (Medical Ethics Committee ‘Twente’, reference number NL50116.044.14/P1426) prospective, stratified and block randomized controlled trial: patients will be allocated to undergo either ACL suture repair or ACL reconstruction. The study will be conducted at the Centre for Orthopaedic Surgery OCON, Hengelo, The Netherlands.

Patients will be recruited at the outpatient department of OCON and informed about the study by their orthopaedic surgeon. After 2–3 days of reflection, an independent investigator will check eligibility and obtain informed consent. One orthopaedic surgeon will operate all patients. Blinding of the surgeon, physiotherapist who will conduct clinimetrics and patient is not used due to practical reasons. All patients will receive identical rehabilitation after surgery, apart from bracing in extension lock for the first 5 days postoperative in the repair group; the standard nationally used physiotherapy protocol regarding ACL reconstruction is given to the patient and their own physiotherapist. Patients will be followed-up in the outpatient clinic preoperatively as well as 6 weeks, 3, 6, 9 months, 1, 2, 5 and 10 years postoperatively (Fig. 1), where all the outcome measurements will be conducted. With weekly data management patients will be contacted in case of no show in order to minimize loss to follow-up. Protocol modifications will be communicated via amendments according to the guidelines of the Medical Ethical Committee.

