### Main study parameter/endpoint

The primary objective of this non-inferiority study is to determine whether ACL repair will result in at least equal effectiveness compared with ACL reconstruction in terms of the self-reported functional outcome measured by the International Knee Documentation Score 2000 subjective knee evaluation score (IKDC Subjective) 1 year postoperative (Table 1) [23–25].

**Table 1 Tab1:** Oversight of the investigations and follow-up moments

	B	OR	6w	3 m	6 m	9 m	1y	2y	5y	10y
X-ray	x	x					x	x	x	x
MRI	x									
IKDC 2000 Subjective	x		x	x	x	x	x	x	x	x
IKDC 2000 Current health	x	x	x	x	x	x	x	x	x	x
IKDC 2000 History	x	x	x	x	x	x	x	x	x	x
IKDC 2000 Demographic form	x	x	x	x	x	x	x	x	x	x
IKDC Physical examination	x		x	x	x	x	x	x	x	x
KOOS	x		x	x	x	x	x	x	x	x
Tegner score	x		x	x	x	x	x	x	x	x
VAS satisfaction	x		x	x	x	x	x	x	x	x
AP laxity	x		x	x	x	x	x	x	x	x
LSI power tests	x				x	x	x	x	x	x
LSI jump tests					x	x	x	x	x	x
Sport specific fatigue test							x			
Concomitant injury		x								
Rupture pattern		x								
Quality repair		x								
Complications & side effects		x	x	x	x	x	x	x	x	x
Re-rupture			x	x	x	x	x	x	x	x

*B* baseline, *OR* peri-operative, *w* weeks, *m* months, *y* years, *IKDC* International Knee Documentation Score, *KOOS* Knee Injury and Osteoarthritis Outcome Score, *VAS* Visual Analog Scale, *AP* anteroposterior, *LSI* leg symmetry index

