#### Descriptive statistics

Baseline characteristics will be presented as mean ± SD or median (range) for continuous data and as numbers with corresponding percentages for categorical data as appropriate. Comparisons between randomized groups will be analysed using X^2^ or Fisher’s exact test for categorical variables and the Student T-test or Mann-Whitney U test for continuous variables, with normality verified by the Shapiro-Wilk test and histograms.

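### The analyst is left unblinded for a reason that argues for blinding, while the primary method is still to be chosen from the data

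*Protocol article*

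**What the plan says.** All references are to the protocol article.

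- **Statistics.** Data are entered and analysed in SPSS "by the trialcoordinator who is not involved in data collection and therefore not blinded to group allocation of participants".
- **Study design.** "Blinding of the surgeon, physiotherapist who will conduct clinimetrics and patient is not used due to practical reasons". The stated ground is practicality, and the analyst is not in this list.
- **Main study parameter/endpoint.** The primary comparison at 1 year is made "in terms of the self-reported functional outcome measured by the International Knee Documentation Score 2000 subjective knee evaluation score", so the patient is the source of the primary data.
- **Primary study parameter.** The method has two branches. The parametric branch reads: "For normally distributed data mixed models analyses for repeated measures will be used". The rank-based alternative is worded as follows: "In case of non-normally distributed data, the Friedman test for differences within groups, and Mann-Whitney Y test for differences between groups, will be used". A further step follows: "In case of non-inferiority, superiority analyses will be conducted".
- **Descriptive statistics.** Baseline comparisons are to be made "with normality verified by the Shapiro-Wilk test and histograms". No cut-off is given.
- **Secondary study parameters.** "Two independent radiologists will evaluate the Kellgren and Lawrence score for radiologic signs of osteoarthritis". Whether these readers are blinded is not stated.
- **Randomization.** An independent investigator carries out the allocation.

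**The concern.** The sentence on the analyst gives a reason and a conclusion that point in opposite directions. Someone who never sees patients or collects their data has no operational need to know who received which operation. The text nevertheless takes this separation as the ground for leaving that person unblinded.

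This matters more here than in many trials for two reasons. First, the people who produce and measure the outcomes already know the allocation, so the analysis is one of the few stages where masking is still possible for the primary endpoint. Second, the analysis is not fully fixed. Whether the primary comparison uses a mixed model or rank tests depends on how the data look, and that decision would be taken by someone who can see which arm it favours. The same decision then carries into the superiority analysis. At stake is the credibility of a non-inferiority claim planned on 20 evaluable patients per group, more than any demonstrable shift in the estimate.

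**Working it through.** The plan gives no figure for this point, so the check is mainly one of reading the statements against each other.

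**1. Does the reason support the conclusion?** Premise (Statistics): the coordinator does not collect data. Conclusion (same sentence): the coordinator is not blinded. Distance from data collection removes an obstacle to blinding and creates none. The inference fails.

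**2. Is there another reason elsewhere?** Study design gives practical reasons for not blinding the surgeon, the physiotherapist and the patient. It does not mention the analyst, and no other section does. The faulty reason is the only one offered.

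**3. Could it be a drafting slip?** The first half of the sentence leads naturally to the statement that the coordinator is blinded. The same sentence calls the data identified, where de-identified may have been meant. Nothing in the article settles this. If it is a slip, the article misreports a safeguard. If it is not, a feasible safeguard is given up for no valid reason. The sentence needs correction either way.

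**4. Is there an analysis choice that knowledge of the arms could influence?** Yes. Primary study parameter makes the method depend on normality and does not say how normality will be assessed. The only procedure named is under Descriptive statistics, for baseline comparisons. It combines a test with visual inspection and has no threshold. Using it for the primary endpoint would be a plausible extension, but the article does not state it.

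**5. How much could such a choice matter?** The documents give no figure. A simulation gives a rough sense of scale under these inputs:

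- 20 per arm and SD 9 (Sample size determination);
- no true difference, one time point, two-sided 0.05, 20,000 simulated trials (assumptions);
- a t-test standing in for the mixed model, against a Mann-Whitney test;
- two outcome shapes: normal, and left-skewed scores bounded at 100 (assumption).

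| Data | t-test rejects | Mann-Whitney rejects | Either rejects |
|---|---|---|---|
| Normal | 4.90% | 4.84% | 5.84% |
| Skewed | 4.93% | 4.96% | 6.45% |

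Monte Carlo standard error near 5%: √(0.05 × 0.95 / 20,000) = 0.15 percentage points.

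The last column is the most that any rule for choosing between these two tests could reach in this setting. The excess over the t-test alone is 5.84 − 4.90 = 0.94 points for normal data and 6.45 − 4.93 = 1.52 points for skewed data. This concerns a test of no difference, as in the superiority step. It does not measure the effect on the non-inferiority comparison against the 10-point margin.

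**The case against.** The strongest reply has four parts.

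**The analyst has little discretion.** A reader might infer that the unblinded coordinator also decides who counts as lost or excluded, and could move the result by keeping or dropping a patient. The documents do not support this. Exclusion at arthroscopy follows the listed criteria during surgery (ACL suture repair; ACL reconstruction). Eligibility is checked by an independent investigator, and no-shows are contacted under weekly data management (Study design). No estimate of bias should be built on discretion over patients. The branch between methods remains.

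**Not everyone else is known to be unblinded.** It is tempting to say that nobody in the trial is blinded. The article names the surgeon, the physiotherapist and the patient, and is silent on the two radiologists. They score only a secondary outcome, so the point about the primary endpoint is unaffected.

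**Data-dependent choice is a separate fault.** Fixing the method in advance would cure it whether or not the analyst is masked. This is correct, and the remedy therefore includes it. The simulation also allows a freedom that the plan does not grant: the plan ties the method to normality, not to the smaller p-value.

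**Masking is harder than it looks and does less than it seems.** The coordinator also enters the data, which include perioperative items such as quality of the repair (Table 1). And for a patient-reported endpoint with unblinded patients, the larger source of bias lies with the patient, where masking the analyst does nothing. Both points stand. They limit the benefit and raise the cost somewhat, but they do not make the printed reason valid.

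**Conclusion.** The point holds as a low-priority correction. The article states affirmatively that the analyst is unblinded, and the reason it gives supports the opposite. This is a statement that is wrong in its logic, so it is not a detail that can be left to a fuller protocol or analysis plan. Combined with a primary method chosen after looking at the data, it means that the choice would be made with the arms known.

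The size of any bias cannot be derived from the documents. The illustration, an excess of about 1 to 1.5 percentage points in false-positive rate for a test of no difference, suggests that it is modest. It rests on a single time point, a t-test in place of the mixed model, an assumed skewed shape, and a freedom of choice wider than the plan allows.

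A reader might also infer that masking would remove the bias. It would only reduce it, since some data can still reveal the arm and the patient's own knowledge of treatment is untouched. If the sentence is a slip, the fault shrinks to misreporting and the wording alone needs repair, but the method should still be fixed before the arms are known.

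**What to change.** First establish whether the coordinator is in fact to be blinded, then replace the sentence in Statistics with something of this kind:

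> The primary IKDC analysis is run on an extract in which the arms are coded A and B and from which arm-revealing variables are left out. The independent investigator who randomises holds the code. The primary method and the analysis set are fixed in writing before the code is opened.

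Arm-revealing variables include time from injury to surgery, quality of the repair, bracing and spring removal. The primary result can be produced as a confidence interval for A minus B and read against the 10-point margin once the code is opened, so the analyst need not know beforehand which direction counts against repair.

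In Primary study parameter, state which method is primary instead of leaving it to a look at normality. This is the more robust half of the change, because it protects the result even where masking is incomplete.

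**Cost.** Recruitment, treatment, visits and sample size do not change. The independent investigator already exists and only has to hold the code. The real burden is that the coordinator enters the data and may recognise patients. Masking is therefore partial unless the extract carries new study numbers or other existing staff enter the arm-revealing forms. If neither is feasible, the article should say so, give that as the reason for not blinding the analyst, and rely on the method fixed in advance.
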